## Abstract

**Background::**

Diarrhea-predominant irritable bowel syndrome (D-IBS) is the main subtypes of irritable bowel syndrome (IBS). In recent years, more than half of IBS patients have received complementary and alternative medicine. Traditional Chinese herbal formula is widely used in Asia, and clinical studies have also found that Chinese herbal formula could significantly improve abdominal pain and diarrhea. We plan to carry out a randomized, controlled, double blind, clinical studies to observe the clinical efficacy of Qinghua Zhixie decoction in the treatment of D-IBS.

**Methods::**

Four hundred sixty-four participants will be randomly assigned to the treatment group and control group. Patients in both groups would take medications and stimulations simultaneously. The outcomes of IBS symptom severity score, quality of life, psychological states, and recurrence rate will be recorded. Statistics will be analyzed with the SPSS 22.0.

**Conclusions::**

The findings of the study will identify the safety and efficacy of Qinghua Zhixie decoction in the treatment of D-IBS.

**Trial registration: OSF Registration number::**

DOI 10.17605/OSF.IO/C8MHW.

## Introduction

1

Irritable bowel syndrome (IBS) is characterized by recurrent abdominal pain, abdominal discomfort, abdominal distension, changes in bowel habits, and abnormal stool.^[1]^ IBS is common to society, with a prevalence of 3% to 20% in the USA, and 5% to 10% in Asia, according to the epidemiological investigation.^[2,3]^ Diarrhea-predominant irritable bowel syndrome (D-IBS) is the main subtypes of IBS and accounts for 40% of all affected individuals.^[4]^ Patients with D-IBS typically suffer from abdominal pain associated with frequent loose stools, and acute diarrhea is a common symptom.^[5]^

The causes of D-IBS are still not clearly defined, and it is generally believed that enteric neuromuscular dysfunction, visceral hypersensitivity, alterations in the composition of fecal microbiota, inflammation, mental and psychological disorders, and dysfunction of the brain-gut axis are involved.^[6,7]^ D-IBS is easy to recur, and there is still no specific treatment against it. At present, individualized symptomatic treatments, including antidiarrheal, improving intestinal motility, antidepressant, supplemented by psychotherapy and diet conditioning can only temporarily relieve individual symptoms, and a large number of patients reportedly discontinued the medications because of dissatisfaction.^[8,9]^ Moreover, many side effects, including head-ache, dizziness, dry mouth, and insomnia, cardiovascular disorders, and ischemic colitis have been reported after long-term use of those medications.^[10]^ In recent years, complementary and alternative medicine (CAM) has become widely accepted in IBS patients, and more than half of D-IBS patients have received CAM.^[11,12]^

Traditional Chinese herbal formula (CHF) is a widely used CAM therapy in Asia, and clinical studies have also found that CHF could significantly improve abdominal pain and diarrhea against D-IBS patients.^[13–15]^ We have been committed to the clinical application of D-IBS with CHF of Qinghua Zhixie decoction (QZD) for a long time, and have achieved innovative effects. The formula consisted of Fengfei Cao (*Pteris multifida Poir*), Dijin Cao (*Elsholtzia Ciliata Hyland*), Bugu Zhi (*Psoralea corylifolia*), Huanglian (*Coptis chinensis*), Muxiang (*Radix Aucklandiae*), Paojiang (*Baked ginger*), Baishao (*Radix paeoniae alba*), Fangfeng (*Radix Saposhnikoviae*), Cangzhu (*Rhizoma atractylodis*), Baizhu (*Rhizoma Atractylodis Macrocephalae*), and Xianhe Cao (*Agrimonia pilosa*). In the formula, berberine, the main active ingredient of Coptis chinensis, can regulate the intestinal flora to improve abdominal pain and diarrhea symptoms in IBS,^[16,17]^ and the combination of Radix Saposhnikoviae, Rhizoma Atractylodis Macrocephalae, and Radix paeoniae alba can improve the imbalanced fecal microbiota, reduce visceral hypersensitivity, and regulate the secretion of brain-gut peptides in patients with D-IBS.^[18,19]^ Therefore, we plan to carry out a randomized, controlled, double blind, and prospective clinical studies to observe the clinical efficacy of QZD compared with pinaverium bromide (PB) in the treatment of D-IBS.

## Method

2

### Study design

2.1

The study is a single-center, double blinded, double doomy, randomized, controlled clinical trial. The study has been approved by the Ethics Committee of Changshu Hospital Affiliated to Nanjing University of Chinese Medicine, and the trial will be carried out in accordance with the Declaration of Helsinki. The clinical trial has been registered on open science framework on January 18, 2022 (Registration number: DOI 10.17605/OSF.IO/C8MHW). The protocol conforms to the Standard Protocol Recommendations for Interventional Trials (SPIRIT) 2013 statement,^[20]^ and the results will be reported according to the CONSORT statement extension for trials.^[21]^ The schedule of enrollment, interventions, and assessments is shown in Table 1.

**Table 1 T1:** Schedule of enrollment, intervention, and assessments.

	Enrollment	Treatment					Follow up
Time point	Week 0	Week 1	Week 2	Week 4	Week 6	Week 8	Week 16
Enrollment							
Eligibility screen	√						
Informed consent	√						
Demographics	√						
History of disease	√						
Allocation	√						
Intervention							
QZD+PB-simulation		√	√	√	√	√	
PB+QZD-simulation		√	√	√	√	√	
Assessments							
IBS-SSS		√	√	√	√	√	√
IBS-QOL	√					√	√
HAMD scale	√					√	√
Recurrence rate							√
Adverse effects				√		√	

HAMD = Hamilton depression, IBS-QOL = irritable bowel syndrome-quality of life questionnaire, IBS-SSS = irritable bowel syndrome symptom severity score, PB = pinaverium bromide, QZD = Qinghua Zhixie decoction.

### Participants

2.2

Participants will be recruited from inpatients in Changshu Hospital Affiliated to Nanjing University of Chinese Medicine, and they will be randomly assigned to either the treatment group and control group by a 1:1 ratio (Fig. 1).

**Figure 1 F1:**
[figure not shown]
Flow diagram of this study.

### Inclusion criteria

2.3

(1)Patients meeting the diagnostic criteria for D-IBS;(2)Patients aged from 18 to 70 years old;(3)Patients without taking any drugs that would influence the results of this study at least 2 weeks before enrollment;(4)Patients with written informed consent.

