### Exclusion criteria

2.4

(1)Patients with other gastrointestinal diseases, such as gastrointestinal tumors, anal diseases, intestinal obstruction, perforation, tumors, and anal diseases;(2)Patients with a history of bowel surgery;(3)Women in pregnancy, lactation, and menstruation;(4)Patients taking non-steroidal anti-inflammatory drugs within 1 month that may affect visceral sensitivity;(5)Patients with a history of allergies or allergic to Chinese herbs.

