#### Primary outcome

2.7.1

Irritable bowel syndrome symptom severity score (IBS-SSS)^[22]^ is the primary outcome to record the degree and frequency of abdominal pain, abdominal distention, defecation satisfaction, and quality of life at weeks 0, 1, 2, 4, 6, 8, with 4 grades: remission (less than 75 points), mild (76–175 points), moderate (176–300 points), and severe (over 300 points).

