#### Secondary outcomes

2.7.2

(1)Quality of life: The IBS-quality of life questionnaire^[23]^ will be applied to to assess the patients’ quality of life with the following aspects: emotional state, psychological state, sleep, energy, daily activities, eating habits, social activities, major activities or work, and sex life, and a higher score reflects a lower quality of life. The questionnaire will be completed before and after treatment.(2)Psychological states: The Hamilton depression scale^[24]^ will be used to evaluate the depressive states of patients during the clinical trial, and the Hamilton Anxiety scale^[25]^ for anxiety. The questionnaires will be completed before and after treatment.(3)Recurrence rate: Patients will be followed up for another 8 weeks after the treatment, and the recurrence will be observed at week 16. If the IBS-SSS of a cured patient changes from remission to mild or a more severe state, he will be considered as recurrence.^[26]^ The recurrence rate = recurrent patients/total follow-up patients × 100%.

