### Sample size

2.10

According to our preliminary experiment, QZD and PB are expected to reduce the IBS-SSS by 115 points and 105 points, respectively. Taking α = 0.05, β = 0.2, SD = 37, 212 cases will be needed in each group. Considering a loss to follow-up of 10%, 464 cases in total will be included.

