### Statistical methods

2.14

Statistics will be analyzed with the SPSS 22.0 (SPSS Inc., Chicago, IL). Statistical testing is 2-sided and *P* < .05 is considered statistically significant. Efficacy outcome parameters will be analyzed on an intent to-treat basis, and the last observation carried forward rule will be applied to manage missing data. The results will be reported in descriptive statistics. According to the homogeneity, group *t* test for normally distributed data or Mann-Whitney *U* test for non-normally distributed data will be used to compare variables between groups.

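### No minimum IBS-SSS is required at entry, so patients already in the plan's own remission grade can be enrolled and dilute the 10-point difference (minor)

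*Protocol article*

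**What the plan says.** Section 2.3 has four inclusion criteria. The only one about the disease is "Patients meeting the diagnostic criteria for D-IBS"; the others concern age, a two-week period without interfering drugs, and consent. Section 2.4 has five exclusions (other gastrointestinal disease, bowel surgery, pregnancy, lactation or menstruation, NSAID use, and allergy). Neither list mentions the IBS-SSS or current symptom severity.

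Section 2.7.1 makes the IBS-SSS the primary outcome, lists it from week 0, and grades it as "remission (less than 75 points), mild (76–175 points), moderate (176–300 points), and severe (over 300 points".

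Section 2.10 sizes the trial on group falls: "QZD and PB are expected to reduce the IBS-SSS by 115 points and 105 points, respectively". It continues: "Taking α = 0.05, β = 0.2, SD = 37, 212 cases will be needed in each group".

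Section 2.7.2 defines recurrence at week 16: "If the IBS-SSS of a cured patient changes from remission to mild or a more severe state". It does not define *cured*, and the denominator is all patients followed up.

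Table 1 ticks the IBS-SSS from week 1 onwards but not at week 0.

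**The concern.** The primary outcome measures symptom reduction, yet nothing in the entry rules ensures that there are symptoms to reduce. A patient scoring below 75 at week 0 is in remission by the plan's own grade and can contribute little to a difference between arms. The sample size leaves no reserve for this, since 212 per arm sits just under 80% power. Enrolment also cannot be repaired at the analysis stage.

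The recurrence outcome is exposed as well. A patient in remission at week 0 and still there at week 8 could be taken as cured. If the score then drifts above the remission grade by week 16, ordinary fluctuation would be recorded as relapse after successful treatment.

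**Working it through.** **Inputs.** From section 2.10: falls of 115 and 105, so a difference of 10; SD 37; α = 0.05; β = 0.2; 212 per arm. From section 2.14: "Statistical testing is 2-sided". Assumed, because the article does not give them: the share f of patients in remission at week 0, no treatment difference among those patients, and a scale floor of 0.

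**1. Reproduce the plan's figure.**
n per arm = 2 × (1.960 + 0.842)² × 37² / 10² ≈ 215. The stated 212 is close to this.
Power at 212: the standard error is 37 × √(2/212) = 3.594, so 10 / 3.594 = 2.783, and Φ(2.783 − 1.960) = 79.5%. The sample size is not miscalculated.

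**2. Room to improve.** With a floor of 0, a score below 75 can fall by less than 75 points, against assumed mean falls of 105 and 115.

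**3. Dilution, SD held at 37.** The difference becomes 10 × (1 − f).

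| f (assumed) | Difference | Difference / 3.594 | Power at 212 per arm | n per arm for 80% |
|---|---|---|---|---|
| 0 | 10.0 | 2.783 | 79.5% | 215 |
| 5% | 9.5 | 2.643 | 75.3% | 239 |
| 10% | 9.0 | 2.504 | 70.7% | 266 |

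**4. If these patients also widen the SD.** Suppose 37 applies to the other patients, whose mean fall is 110 (midway between 105 and 115), and the remission patients have mean fall m and SD 20. Then
SD² = (1 − f) × 37² + f × 20² + f(1 − f) × (110 − m)².

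- m = 40, f = 5%: SD = √(1300.6 + 20 + 232.8) = 39.4, power 70%.
- m = 40, f = 10%: SD = √(1232.1 + 40 + 441) = 41.4, power 61%.
- m = 0, f = 5%: SD = √(1300.6 + 20 + 574.8) = 43.5, power 61%.
- m = 0, f = 10%: SD = √(1232.1 + 40 + 1089) = 48.6, power 48%.

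**5. Do the harsher cases fit the plan's own SD?** Read 37 as the SD of the whole sample, which is how section 2.10 presents it. A share f at exactly zero change then leaves the rest with SD² = [37² − f(1 − f) × 110²] / (1 − f). For f = 5% this is (1369 − 574.8) / 0.95, an SD of about 29. For f = 10% it is (1369 − 1089) / 0.90, an SD of about 18. Such a spike sits poorly with a stated SD of 37, so step 3 is the main estimate and step 4 shows how far power could fall under stronger assumptions.

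**The case against.** **The share may be near zero.** Recruitment is from inpatients who meet D-IBS criteria and have been free of interfering drugs for two weeks, and the introduction describes such patients as typically symptomatic. Mean falls above 100 also imply typical baselines well above 75. This stands, and it is the main reason for the minor rating. It does not remove the point, because the text does not exclude these patients. If they are rare, the criterion costs almost nothing.

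**The pilot may already include them.** Section 2.10 takes its falls from a preliminary experiment. If that had similar entry rules, the 10 points may already be diluted. The article does not say, so the further loss in step 3 is possible but not established.

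**The group means are not patient targets.** A reader might infer that every patient must be able to fall by 105 points and that patients below 75 are wrongly enrolled for that reason. The documents do not support this. By that logic baselines of 76 to 104 would fail too, yet they fall in the mild grade and a cut just above remission would admit them.

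**Nobody is declared cured by the text.** A reader might infer that patients in remission at week 0 count as cured. Section 2.7.2 does not say so. The term is undefined, the reading is only possible, and the recurrence denominator is all followed-up patients, not a cured group.

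**No bias arises.** Allocation is 1:1 and double-blind with an intention-to-treat analysis, so low scorers are expected equally in both arms. This stands. Broad entry is also defensible on grounds of generalisability.

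**Conclusion.** The point holds as a minor design weakness. The printed entry lists allow patients already in the plan's remission grade, and these patients have little room to move on the primary outcome. The expected effect is a smaller mean difference and some loss of power: from 79.5% to about 75% or 71% for assumed shares of 5% or 10%, with the SD held at 37 and no treatment difference among these patients. Powers of 61% and 48% can be derived, but only by assigning 37 to the other patients and assuming no mean change in the remission patients; they should not be read as the expected loss. The actual share is unknown. On recurrence, the gap is the undefined term, which leaves room for counting a relapse in someone who never improved.

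**What to change.** 1. Add to section 2.3 a week-0 IBS-SSS above the plan's own remission grade (76 points or more, at least mild), scored before randomisation. Whether to set any higher cut is for the sponsor.
2. Tick the IBS-SSS at week 0 in Table 1, so that it agrees with section 2.7.1 and the criterion can be applied.
3. In section 2.7.2, count recurrence only in patients who were outside remission at week 0 and in remission at week 8.

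No new instrument or visit is needed, and the planned sample size can stand. The cost is that a few patients with minimal symptoms are not enrolled, which narrows generalisability slightly.

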### Exclusion criteria

2.4

(1)Patients with other gastrointestinal diseases, such as gastrointestinal tumors, anal diseases, intestinal obstruction, perforation, tumors, and anal diseases;(2)Patients with a history of bowel surgery;(3)Women in pregnancy, lactation, and menstruation;(4)Patients taking non-steroidal anti-inflammatory drugs within 1 month that may affect visceral sensitivity;(5)Patients with a history of allergies or allergic to Chinese herbs.

### Dropout criteria

2.5

Patients will be dropped if they are with the following conditions:

(1)With severe adverse events (AEs);(2)Unwilling to continue the study protocol.

### Interventions

2.6

#### Treatment group

2.6.1

Patients in the treatment group will take Chinese herbal formula QZD, which is composed of Fengfei Cao (*Pteris multifida Poir*) 30 g, Dijin Cao (*Elsholtzia Ciliata Hyland*) 15 g, Bugu Zhi (*Psoralea corylifolia*) 15 g, Huanglian (*Coptis chinensis*) 2 g, Muxiang (*Radix Aucklandiae*) 6 g, Paojiang (*Baked ginger*) 6 g, Baishao (*Radix paeoniae alba*) 15 g, Fangfeng (*Radix Saposhnikoviae*) 10 g, Cangzhu (*Rhizoma atractylodis*) 10 g, Baizhu (*Rhizoma Atractylodis Macrocephalae*) 15 g, and Xianhe Cao (*Agrimonia pilosa*) 12 g (the ingredients of each herb are provided in Supporting Material 1). The herbs are provided as herbal concentrate-granules in 1 bag and quality controlled by Tianjiang Pharmaceutical Co., Ltd. (Jiangyin, China). Patients will orally take 100 mL of the QZD twice a day and PB-simulation 50 mg 3 times a day continuously for 8 weeks.

#### Control group

2.6.2

Patients in control group will take PB (50 mg, Abbott Products SAS, H20110220) 50 mg 3 times a day and QZD-simulation 100 mL twice a day continuously for 8 weeks.

### Outcome variables

2.7

Patients will be asked to use a diary to record daily stools emissions, symptoms, frequency, and severity of AEs, and use of rescue medication.

#### Primary outcome

2.7.1

Irritable bowel syndrome symptom severity score (IBS-SSS)^[22]^ is the primary outcome to record the degree and frequency of abdominal pain, abdominal distention, defecation satisfaction, and quality of life at weeks 0, 1, 2, 4, 6, 8, with 4 grades: remission (less than 75 points), mild (76–175 points), moderate (176–300 points), and severe (over 300 points).

#### Secondary outcomes

2.7.2

(1)Quality of life: The IBS-quality of life questionnaire^[23]^ will be applied to to assess the patients’ quality of life with the following aspects: emotional state, psychological state, sleep, energy, daily activities, eating habits, social activities, major activities or work, and sex life, and a higher score reflects a lower quality of life. The questionnaire will be completed before and after treatment.(2)Psychological states: The Hamilton depression scale^[24]^ will be used to evaluate the depressive states of patients during the clinical trial, and the Hamilton Anxiety scale^[25]^ for anxiety. The questionnaires will be completed before and after treatment.(3)Recurrence rate: Patients will be followed up for another 8 weeks after the treatment, and the recurrence will be observed at week 16. If the IBS-SSS of a cured patient changes from remission to mild or a more severe state, he will be considered as recurrence.^[26]^ The recurrence rate = recurrent patients/total follow-up patients × 100%.

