### Follow-up

2.9

After 8-week treatment, the patients will be followed-up for another 8 weeks to assess the recurrence rate.

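### The recurrence rate registers loss of benefit only in patients who reached remission, so it is a poor sole follow-up measure of whether the effect lasts

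*Protocol article*

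**What the plan says.** All references are to the protocol article.

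- Section 2.7.2 (3) defines the event: "If the IBS-SSS of a cured patient changes from remission to mild or a more severe state, he will be considered as recurrence". It then gives the formula: "The recurrence rate = recurrent patients/total follow-up patients × 100" per cent.
- Section 2.7.1 sets the grades: "remission (less than 75 points), mild (76–175 points), moderate (176–300 points), and severe (over 300 points"). The same section places the primary IBS-SSS "at weeks 0, 1, 2, 4, 6, 8", which does not include week 16.
- Section 2.9 gives the purpose of the off-treatment period: "the patients will be followed-up for another 8 weeks to assess the recurrence rate".
- Table 1 schedules IBS-SSS, IBS-QOL and HAMD at week 16, without limiting them to patients in remission.
- Section 2.10 gives the expected effect: "QZD and PB are expected to reduce the IBS-SSS by 115 points and 105 points, respectively".
- Section 2.3 sets no minimum or maximum IBS-SSS for entry, and no expected baseline mean is given anywhere.

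**The concern.** The introduction describes D-IBS as prone to relapse, so what happens after treatment stops is a question the trial itself raises. The text answers it with one defined efficacy outcome, and a patient who was not in remission cannot have that event. Such a patient still sits in the denominator and is scored as a non-recurrence, even if every point gained on treatment is lost.

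Two things follow. The rate says little about durability in patients who improved without remission, who may be the majority. And because the denominator is everyone followed up, an arm with few remissions tends to have a low rate for that reason alone, so the rate mixes how often remission was reached with how often it was lost.

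**Working it through.** **The plan's own figure.** No figure is stated for the recurrence rate. The only related figure is the sample size, which supplies the falls and the SD used below: "Taking α = 0.05, β = 0.2, SD = 37, 212 cases will be needed in each group", and "Statistical testing is 2-sided" (section 2.14). The difference is 115 − 105 = 10 points.

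n per group = 2 × (1.960 + 0.842)² × 37² / 10² ≈ 215.

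The stated 212 is within 3% of this and has power of about 79.5%. Adding 10% loss gives 212 / 0.9, or 236 per group and 472 in total, against the stated 464, also within 3%. The inputs are therefore used coherently, and nothing below changes the sample size.

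**Step 1: who can have the event.** I read a cured patient as one in remission (IBS-SSS below 75) at week 8. The baseline from which the average patient ends below 75 is:

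- QZD: below 75 + 115 = 190
- PB: below 75 + 105 = 180

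Both limits are at the bottom of the moderate grade, which starts at 176.

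**Step 2: two patients under the definition.**

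| Week 0 | Week 8 | Week 16 | Change off treatment | Scored as |
|---|---|---|---|---|
| 300 | 185 | 300 | +115, the full planned QZD gain lost | not recurrent |
| any | 74 | 76 | +2 | recurrent |

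**Step 3: chance of remission from a fixed baseline.** Assume that SD 37 is the SD of the reduction (section 2.10 does not say), that falls are normal, and that they do not depend on baseline. Then P(week-8 score < 75) = Φ((75 − (baseline − fall)) / 37).

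| Baseline | Fall 105 (PB) | Fall 115 (QZD) |
|---|---|---|
| 200 | Φ(−20/37) = 29% | Φ(−10/37) = 39% |
| 240 | Φ(−60/37) = 5% | Φ(−50/37) = 9% |
| 300 | about 0.1% | about 0.1% |

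**Step 4: share in remission across a population.** Assume a baseline SD of 60 (not in the document) and a fall of 110, midway between the arms. The SD of the week-8 score is √(60² + 37²) = 70.5.

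| Assumed baseline mean | In remission at week 8 | Cannot have the event |
|---|---|---|
| 200 | Φ(−15/70.5) = 42% | 58% |
| 250 | Φ(−65/70.5) = 18% | 82% |
| 300 | Φ(−115/70.5) = 5% | 95% |

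**Step 5: sensitivity.** Let the SD of the week-8 score run from 37 to 80 instead.

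| Assumed baseline mean | QZD in remission | PB in remission |
|---|---|---|
| 180 | 55–61% | 50% |
| 200 | 39–45% | 29–40% |
| 250 | 5–23% | 3–19% |
| 300 | 0.1–8.5% | 0.1–6.7% |

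Only a population with a mean near 180 or lower puts half or more of the patients at risk of the event.

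**Step 6: effect of the denominator.** Suppose 40% (QZD) and 30% (PB) reach remission and half of them relapse in each arm. The defined rates are 0.40 × 0.5 = 20% and 0.30 × 0.5 = 15%. The arm with more remissions looks worse, although the relapse risk among remitters is 50% in both.

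**The case against.** A reader might infer that patients who improve without remission are invisible and that the follow-up cannot show whether benefit lasts. The document does not support that. Table 1 schedules IBS-SSS, IBS-QOL and HAMD at week 16 for everyone, so a 300–185–300 course would be recorded, and section 2.14 provides a between-group test that could be applied to it. The limitation lies in the outcome that the text defines, not in the data.

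Three further objections deserve weight.

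- Restricting recurrence to patients who had been in remission is the ordinary meaning of the word, and the definition carries a citation. This stands: the measure is legitimate as a description. The fault is that sections 2.7.2 and 2.9 make it the only defined efficacy outcome of the follow-up.
- A low rate caused by few remissions is largely a product of the denominator. This also stands. Dividing by remitters would remove that distortion, but it would still leave out partial responders and would compare subsets selected after randomisation.
- The size rests on a baseline distribution that the document does not give, and mild patients may enter. This stands too, and it is why the result is a range.

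It can also be said that an article leaves the list of week-16 contrasts to the full protocol or analysis plan. That is fair for detail. Here, however, the event, the formula and the purpose of follow-up are all fixed in the text, section 2.7.1 stops the IBS-SSS at week 8, and section 2.7.2 describes the questionnaires as completed only before and after treatment.

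**Conclusion.** The point holds in a limited form. As defined, recurrence can occur only in patients who reached an IBS-SSS below 75, and those who improved without remission and relapsed are counted as non-recurrent. At the planned falls, the average patient qualifies only from a baseline below about 180 to 190. With assumed baseline means of 200 to 300 and SD 60, roughly 58% to 95% of patients cannot have the event; near a mean of 180 the share is about half or somewhat less. These shares depend on the assumed baseline distribution, on normality, and on reading SD 37 as the SD of the reduction. The definition and the 180 to 190 limits do not.

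The rate is therefore a poor measure of durability. It concerns a secondary outcome, leaves the primary outcome and the sample size untouched, and can be put right with measurements already scheduled.

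**What to change.** - In sections 2.7.2 and 2.9, name the between-arm difference in week-16 IBS-SSS, and in the change from week 8 to week 16, in all randomised patients as the durability outcome.
- Reconcile section 2.7.1 with Table 1, so that the text lists the week-16 IBS-SSS that the table schedules. Table 1 also leaves week 0 unticked for IBS-SSS although section 2.7.1 lists it; both can be corrected together.
- Keep remission-based recurrence as a supplementary description, reported by arm next to the number in remission at week 8, so that the reader can see how many patients could have the event.
- State how missing week-16 scores are handled. Under the last-observation rule in section 2.14, a missing week-16 score would be replaced by an on-treatment value, which assumes that the gain was kept.

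An additional event based on worsening by a severity grade is not recommended. A 300–190–300 course stays within the moderate grade throughout, and requiring prior improvement would again select patients on post-randomisation response.

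The cost is a change of wording and one more secondary comparison. No visit, measurement or patient is added.

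### The recurrence rate counts only patients who leave remission but divides by everyone followed, so it mixes remission with relapse and can point the wrong way

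*Protocol article*

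**What the plan says.** Section 2.7.2 of the protocol article, item (3), fixes both parts of the ratio. The event is limited to remitters: "If the IBS-SSS of a cured patient changes from remission to mild or a more severe state, he will be considered as recurrence". The denominator is not: "The recurrence rate = recurrent patients/total follow-up patients".

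The timing is given in the same item: "Patients will be followed up for another 8 weeks after the treatment, and the recurrence will be observed at week 16". Section 2.9 (Follow-up) describes the group in general terms: "the patients will be followed-up for another 8 weeks to assess the recurrence rate". Table 1 schedules the IBS-SSS at weeks 8 and 16 with no restriction to patients in remission.

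The grades come from section 2.7.1, where the two lowest are given as "remission (less than 75 points), mild (76–175 points". For planning, section 2.10 states that "QZD and PB are expected to reduce the IBS-SSS by 115 points and 105 points, respectively", with an SD of 37. No expected remission or recurrence proportion appears anywhere.

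**The concern.** A patient who never reached remission cannot recur under this definition, yet is counted below the line as if free of recurrence. The quantity therefore depends on two things: how many patients a treatment brings into remission, and how many of those relapse. More remissions push it up, although that is a benefit. In the limit, an arm with no remissions would score 0% recurrence.

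Recurrence is named among the outcomes in the abstract, and assessing it is the only purpose given for the 8-week follow-up in section 2.9. As defined, the rate cannot separate durability from initial response, and the comparison between arms may have the wrong sign.

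**Working it through.** **Formula.** Let r be the proportion in remission at week 8 and q the risk that a remitter is out of remission at week 16. The protocol names no week for being cured. Week 8, the end of treatment, is inferred from the follow-up period. With complete follow-up:

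- rate as defined = r × q
- relapse risk among those who can relapse = q
- sustained remission among all patients = r × (1 − q)

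If q is equal in the two arms, the ratio of the defined rates equals the ratio of the remission proportions. The QZD arm shows the lower rate only if q(QZD) < q(PB) ÷ [r(QZD) ÷ r(PB)].

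**The plan's own figure.** There is no recurrence figure to reproduce. The planning inputs used below are the 10-point difference (115 − 105) and SD 37. They give 2 × (37 × (1.96 + 0.84) / 10)² = 214.7, or 215 per arm. The stated 212 is within 3% of this.

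**Remission implied by the planned effect.** Assume that week-8 scores are normal, that the SD of 37 applies to them, and that QZD scores are 10 points lower. The shift is 10/37 = 0.27 SD, so r(QZD) = Φ(Φ⁻¹(r(PB)) + 0.27). For r(PB) = 40%: Φ(−0.253 + 0.270) = 50.7%.

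**Rate as defined, with true relapse of 30% in both arms and 212 followed per arm:**

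| PB remission (assumed) | QZD remission | Rate as defined, QZD vs PB | Ratio | P | Break-even QZD relapse | Sustained remission, QZD vs PB |
|---|---|---|---|---|---|---|
| 20% | 28.4% | 8.5% vs 6.0% | 1.42 | about 0.32 | 21.1% | 19.9% vs 14.0% |
| 40% | 50.7% | 15.2% vs 12.0% | 1.27 | about 0.34 | 23.7% | 35.5% vs 28.0% |
| 60% | 70.0% | 21.0% vs 18.0% | 1.17 | about 0.44 | 25.7% | 49.0% vs 42.0% |

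In the middle row, the rate is 0.507 × 0.30 = 15.2% against 0.40 × 0.30 = 12.0%. Break-even is 0.30 × 0.40 / 0.507 = 23.7%. Sustained remission is 0.507 × 0.70 = 35.5% against 0.40 × 0.70 = 28.0%.

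**Direction when QZD truly relapses less (25% vs 30%).** At 40% PB remission the formula gives 0.507 × 0.25 = 12.7% against 12.0%, which is the wrong direction. At 60% it gives 0.70 × 0.25 = 17.5% against 18.0%, the right direction but with a true 5-point advantage reduced to 0.5 points.

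**The case against.** A reader might infer that the arm curing more patients must look worse. The protocol does not support that. Once that arm's relapse risk falls below the break-even value, its rate as defined is lower. At 50.7% vs 40% remission and 15% vs 30% relapse, the formula gives 7.6% vs 12.0%, in the right direction.

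A reader might also infer a large distortion. Remission of 60% vs 40% with 30% relapse in both arms would give 18% vs 12%. Under the same normal model, however, that gap needs about 2 × 0.253 × 37 = 19 points, nearly twice the planned difference. At the planned effect the spurious difference is about 2 to 3 percentage points and would usually not be significant.

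The other objections concern weight. Recurrence is a secondary outcome, so the primary outcome, sample size and randomisation are untouched. The week-8 and week-16 scores are collected in any case, so a rate among remitters could be computed even if the text stayed as it is. All of this stands. It limits the severity but does not repair the formula: no other section corrects the denominator, and reading it as cured patients only does not fit section 2.9 or Table 1.

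Nor is dividing by remitters a complete answer. They are a subset formed after randomisation, so a comparison between arms within it is not protected by randomisation.

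**Conclusion.** The definition is wrong as written and should be fixed, as a problem of moderate weight in a secondary outcome. The mismatch between event and denominator follows from the text alone.

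Its size depends on assumptions, because the protocol states neither remission nor relapse rates. With the planned 10-point difference, SD 37 applied to normal week-8 scores, complete follow-up, 30% relapse in both arms and 20% to 60% PB remission, the formula produces an excess of about 2.5 to 3.2 percentage points against the arm with more remissions. A modest true advantage in relapse may be hidden or reversed; a large one would still show. The evidence supports a measure that can mislead on durability. It does not support a claim that the conclusion will be reversed.

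Separately, and minor: remission is below 75 and mild begins at 76, so a score of exactly 75 has no grade. Recurrence is judged across this boundary, but only one score value is affected, and the denominator argument does not depend on it.

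**What to change.** Change section 2.7.2, item (3), before unblinding:

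1. **Descriptive recurrence rate.** Patients in remission at week 8 who are not in remission at week 16, divided by patients in remission at week 8 who have a week-16 score. Name week 8 explicitly as the point at which remission is judged.
2. **Comparison between arms.** Sustained remission, meaning remission at both week 8 and week 16, among all randomised patients, as a risk difference with a 95% confidence interval.
3. **Missing week-16 scores.** Count them as not sustained, with a sensitivity analysis under other assumptions. The last-observation-carried-forward rule in section 2.14 should not apply here, because it would turn a week-8 remitter lost to follow-up into a sustained remission.
4. **Score of exactly 75.** The authors should assign it to one grade in section 2.7.1.

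Cost: no extra visits or measurements. The change does add a newly defined comparison and a missing-data rule, so it is more than a change of wording. The descriptive rate rests on fewer patients. At 40% remission, 0.40 × 212 is about 85 patients, and a 30% rate has a 95% half-width of about 1.96 × √(0.30 × 0.70 / 85) = 9.7 points. The present formula's 12% of 212 has about 1.96 × √(0.12 × 0.88 / 212) = 4.4 points. The descriptive rate is also not a randomised comparison and should be labelled so. Counting missing as not sustained may mix loss to follow-up with relapse if loss differs between arms, which is why the sensitivity analysis is needed.
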